### **10.2 Planned recruitment rate**

An estimated 3 individuals will be recruited per month over a 21 month period. This takes into account the following factors:

- The estimated prevalence of NAFLD amongst HIV-infected cohorts is predicted to be 30%. Although a large proportion of these individuals are likely to remain undiagnosed in the absence of a NAFLD screening programme, recruitment at several sites with > 5000 HIV-infected patients overall is expected to yield at least 200 who have been diagnosed with NAFLD on previous imaging as part of routine clinical care
- All HIV-infected patients are expected to attend a minimum of two medical appointments per year. For a minimum of 5000 HIV-infected patients, a monthly target of 4-5 is predicted to be feasible, allowing for 1-2 screen failures per month leaving 3-4 recruited per month.

### **10.3 Statistical analysis plan**

#### **10.3.1 Summary of baseline data and flow of patients**

Baseline comparability between the randomised groups (maraviroc-allocated, versus non-maraviroc allocated,) will be described by considering the variables below.

For categorical data, % will be presented.

For continuous data, mean or median will be presented for variables following a normal and non-normal distribution, respectively, in addition to the interquartile range (IQR).

Age (IQR)

% male

% each ethnicity

Duration of HIV infection (IQR)

Nadir CD4 count (IQR)

Baseline CD4 count (IQR)

% with undetectable HIV VL

% receiving PI-based cART vs non-PI based cART

% receiving concomitant lipid lowering therapy

BMI (IQR)

Waist circumference (IQR)

Weight (IQR)

BP (IQR)

Fasting glucose (IQR)

HbA1c (IQR)

Bilirubin (IQR)

ALT (IQR)

Fasting TG (IQR)

Fasting LDL (IQR)

Fasting HDL (IQR)

Fasting total cholesterol (IQR)

Fasting HDL:chol ratio (IQR)

Baseline ELF score (IQR)

Baseline Fibroscan stiffness result (IQR)

Baseline Fibroscan CAP score (IQR)

% with a CT liver:spleen attenuation ratio <1.0

Baseline diet score (IQR)

See Figure 1 for the CONSORT flow diagram for this study.

[figure not shown]

Figure 1. HEPMARC Flow Diagram

[figure not shown]

Citation: Eldridge SM, Chan CL, Campbell MJ, Bond CM, Hopewell S, Thabane L, et al. CONSORT 2010 statement: extension to randomised pilot and feasibility trials. *BMJ*. 2016;355.  
HEPMARC Consort Flow Diagram v1.0

Figure 1: CONSORT flow diagram for the HEPMARC study.

### 10.3.2 Feasibility Outcome analyses

All analyses will be performed on available cases according to intention to treat (ITT) principles. Therefore, all individuals randomised within the study (including those subsequently withdrawn) will be included in outcome analyses.

The following analyses will be presented:

- a) Proportion of eligible individuals approached who are successfully recruited  
It is envisaged that a recruitment rate of at least 50% will be achieved. This takes into account the likelihood that a proportion of potential recruits will decline particularly owing to the requirement for twice daily pill taking.
- b) Monthly participant recruitment rate. This is expected to be a minimum of at least 2 participants consistently per month, with an average of 3-4.
- c) Participant retention in the study at 48 and 96 weeks in the maraviroc and non-maraviroc assigned groups. This is expected to be at least 65% (cf 35% discontinuation in the MOTIVATE study [9]).
- d) Proportion of participants for whom there is missing data at 48 and 96 weeks in the maraviroc and non-maraviroc assigned groups. This is expected to be less than 20% for all participants.
- e) Proportion of participants reporting adverse events at 48 and 96 weeks in the maraviroc and non-maraviroc assigned groups. This is expected to be less than 10% [18].
- f) Level of self-reported adherence to the study drug at 48 and 96 weeks in those allocated to the maraviroc group. This is expected to be greater than 90%.

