### **9.3 Recording and reporting of AEs, ARs, SAEs, SARs AND SUSARs**

All AEs, ARs, SAEs, SARs and SUSARs will be documented in the eCRF.

The adverse event reporting period will be from consent until the subject's final study visit. In addition, any untoward event that may occur subsequent to the reporting period that the Investigator assesses as possibly, probably or definitely related to the study drug medication will also be reported as an Adverse Reaction.

AEs, ARs, SAEs, , SARs and SUSARs may be directly observed, reported spontaneously by the subject or by questioning the subject at each study visit. These will be followed up until they are resolved or the

subject's participation in the study ends (i.e. until the final eCRF is completed for that subject). In addition, all serious adverse events assessed by the Investigator as possibly related to the investigational medication should continue to be followed even after the subject's participation in the study is over.

Such events should be followed until resolution, or until no further change can reasonably be expected. Deaths occurring more than 30 days after the final dose, which are considered to be unrelated to the study medication, should not be reported as a Serious Adverse Event.

SAEs should be reported immediately to the BSCTU.

All **SAEs** occurring from the time of **consent** until **30** days post cessation of trial treatment must be recorded on the SAE Form and emailed to the BSCTU immediately at [[contact]](mailto:[contact]), at least **within 24 hours** of the research staff becoming aware of the event.

For each **SAE** the following information will be collected:

- full details in medical terms and case description
- event duration (start and end dates, if applicable)
- action taken
- outcome
- seriousness criteria
- causality (i.e. relatedness to trial drug / investigation), in the opinion of the investigator
- whether the event would be considered expected or unexpected in relation to the Reference Safety Information.

Any change of condition or other follow-up information should be emailed to the Sponsor as soon as it is available or at least within 24 hours of the information becoming available. Events will be followed up until the event has resolved or a final outcome has been reached.

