## **10 STATISTICS AND DATA ANALYSIS**

### **10.1 Sample size calculation**

This is a pilot study to evaluate the feasibility and potential efficacy of addition of maraviroc to optimised background combination antiretroviral therapy and therefore no formal sample size calculation has been conducted. Results may be used to estimate the variability of the treatment effect of MVC on the ELF score which in turn may inform the sample size calculation for a larger placebo-controlled RCT.

In a previous biopsy study, a unit increase of 1 in the ELF score was associated with a 2.5-fold increased risk of a liver-related event (adjusted for age and stage of fibrosis) and therefore a unit increase of 1 is deemed to represent a clinically important entity [24]. Assuming the SD of the ELF score is 1.12, with 20 patients in each group for the analysis, a difference in ELF of 1 point can be estimated with a 95% confidence interval from 0.6 to 1.4. Assuming an attrition rate of 33%, a target of 30 individuals will be recruited per group [23].

A t-method will be used to estimate the difference in ELF scores, together with 95% confidence intervals, between the two groups. P-values will not be presented.

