#### **10. 4 Procedure(s) to account for missing or spurious data**

In the event of missing data, only available data will be included in the analyses.

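### The primary adverse-event measure is a crude proportion with an unsettled denominator and no allowance for unequal follow-up; with everyone randomised as denominator, it falls as drop-out rises

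*Protocol*

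**What the plan says.** Protocol 3.3 lists adverse events among the primary measures, and 10.3.2 item (e) gives the analysis: "Proportion of participants reporting adverse events at 48 and 96 weeks in the maraviroc and non-maraviroc assigned groups". The item names no denominator and has no rule for people who leave before week 48 or 96. It adds an expectation that the figure will be below 10%.

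Three statements bear on who is counted:

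- 10.3.2, opening sentence: "All analyses will be performed on available cases according to intention to treat (ITT) principles".
- 10.3.2, next sentence, offered as the consequence of the first: "all individuals randomised within the study (including those subsequently withdrawn) will be included in outcome analyses".
- 10.4: "In the event of missing data, only available data will be included in the analyses".

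On collection, 9.3 says: "The adverse event reporting period will be from consent until the subject's final study visit". Events judged drug-related are still reported after that, and serious events are recorded to 30 days after treatment stops. Table 1 lets screening, where consent is taken, fall up to 42 days before baseline. On loss, 10.1 assumes 33% attrition, and 10.3.2(c) expects retention of at least 65%, which allows up to 35% loss.

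**The concern.** A crude proportion at 96 weeks is a sound estimate of 96-week risk when everyone is watched for 96 weeks. Here up to about a third may not be. Non-serious events not judged drug-related are no longer collected once a participant has made the final visit.

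With everyone randomised in the denominator, a participant who leaves event-free at week 24 stays in the denominator at week 96, with 72 unobserved weeks contributing nothing to the numerator. The measure therefore improves as drop-out rises, and the arm that loses more people looks safer. Drop-out need not be equal: 8.11 makes withdrawal from the study likely when maraviroc compliance is under 80%, a route that exists in one arm only.

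Reading the rule as only those still present does not cure this. Section 7.7 allows withdrawal for toxicity, so people who left because of an event would vanish from both numerator and denominator.

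The collection window also opens before allocation. Unless excluded, screening-period events enter the arm totals although they cannot depend on treatment.

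**Working it through.** **Inputs.** Attrition d = 0.33 (10.1) or 0.35 (1 − 0.65, from 10.3.2(c)); follow-up 96 weeks; expectation below 10% (10.3.2(e)). As a check on the attrition figure, 20/(1 − 0.33) = 29.9, which rounds up to the protocol's 30 per group. The protocol gives no figure for the effect of attrition on measure (e), so what follows rests on assumptions.

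**Assumptions.** "At 96 weeks" is taken as cumulative to week 96. The first-event hazard is constant, h = −ln(1 − F)/96 for a true proportion F. Nothing is captured after leaving. The denominator is everyone randomised.

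**Leaving spread evenly over 96 weeks.** Observed = (1 − d)F + d × [1 − F/(96h)]. For F = 0.10, 96h = 0.1054 and the bracket is 0.0509.

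- d = 0.33: 0.0670 + 0.33 × 0.0509 = 0.084 (relative loss 16.2%).
- d = 0.35: 0.0650 + 0.35 × 0.0509 = 0.083 (17.2%).

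**Leaving at a constant hazard,** m = −ln(1 − d)/96. Observed = h/(h + m) × [1 − (1 − F)(1 − d)].

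- d = 0.33: 0.1054/(0.1054 + 0.4005) × (1 − 0.90 × 0.67) = 0.083 (17.3%).
- d = 0.35: 0.1054/(0.1054 + 0.4308) × (1 − 0.90 × 0.65) = 0.082 (18.4%).

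**Other true proportions, constant leaving hazard, d = 0.35.** 12% reads 9.8%; 50% reads 41.6%.

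**Week 48.** With a true 48-week proportion of 10%, the reading is 9.0–9.2%, a relative loss of 8–10%.

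**Sensitivity to timing (week 96, true 10%, d = 0.33 to 0.35).**

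| Pattern | Relative loss |
|---|---|
| All leavers go at week 4 | 32–33% |
| All at week 24 | 24–26% |
| All at week 48 | 16–17% |
| All at week 72 | about 8% |
| Events spread over the first 24 weeks only, leaving even | about 4% (d × 12/96) |

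**Unequal loss (illustrative split, not from the protocol).** With the same true 50% in both arms and 35% versus 10% attrition at constant hazards, the arms read 41.6% and 47.7%, about 6 points apart with no true difference.

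**Pre-randomisation window.** Six further weeks at the same hazard and full follow-up give 1 − (1 − F)^(102/96). A true 10% becomes 10.6%, and 50% becomes 52.1%.

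**The case against.** The strongest reply is that the denominator is not fixed as everyone randomised, because the sentence before that statement says available cases and 10.4 repeats it. This stands, and it is why the point concerns an ambiguous denominator rather than a fixed one. It does not remove the problem, since each reading has its own bias.

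A reader might also infer that early leavers simply count as event-free. They do not: events up to leaving are recorded, and only later time is lost. If leavers did count as event-free throughout, the loss would be the full 33–35%.

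Several provisions reduce the loss. Section 7.6 requests an early termination visit, 7.7 seeks to retain those who stop the drug and to follow up those withdrawn, and 9.3 keeps some later capture. The figures above assume none of this succeeds.

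The consequences are modest. The 10% figure is an expectation with no decision rule attached, so a true 12% reading 9.8% passes no formal test; that shift is about 0.7 of a participant in 30 (0.022 × 30). No test of (e) between arms is planned, and the 6-point example has a standard error of about 13 points with 30 per arm. Retention by arm, measure (c), will be reported alongside.

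Finally, adverse-event denominators and onset rules are often left to a separate analysis plan. But 10.3 is itself headed as the statistical analysis plan and states a crude summary with conflicting population wording. The point is about what it states, not what it omits.

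**Conclusion.** The point holds as a weakness in how a primary measure is specified. Measure (e) takes no account of unequal follow-up, and 10.3.2 and 10.4 leave its denominator open. With everyone randomised as denominator, the week-96 proportion is understated by roughly 16–18% in relative terms at a true 10%, and by about half that at week 48. This requires 33–35% loss spread evenly or at a constant hazard, a constant event hazard, and no capture after leaving. Other timings give roughly 4–33%, and successful follow-up of leavers would shrink it further. The direction is the same throughout. With only those present counted, the figure is sound only if leaving has nothing to do with having had an event.

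The documents do not support treating one-sixth as a protocol figure, or treating the 10% expectation as a pass mark that attrition would help the trial meet. Nor do they say that pre-randomisation events will be counted in (e), only that they are collected and not excluded.

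**What to change.** In 10.3.2(e):

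- State the denominator and reconcile the wording with 10.4.
- Count events with onset from randomisation in both arms, and list earlier events separately.
- Keep the crude n/N, and add the Kaplan-Meier proportion with a first event at weeks 48 and 96, censored at last contact, with 95% confidence intervals.
- Add events per observed person-years by arm.
- Read the below-10% expectation against the time-to-event figure.

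The Kaplan-Meier estimate keeps people who had an event and then left, and stops crediting unobserved time as event-free. The change is to analysis wording only: 9.2 already records event onset dates and 7.7 withdrawal dates. The cost is a slightly higher reported figure and an assumption that leaving is unrelated to later event risk, which should be stated beside the result.

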### 3.3 Outcome measures/endpoints

#### **Primary endpoint:**

The primary objective will be assessed with respect to the following measures:

- a) Proportion of eligible individuals approached who are successfully recruited
- b) Monthly participant recruitment rate
- c) Participant retention in the study at 48 and 96 weeks in the maraviroc and non-maraviroc assigned groups
- d) Proportion of participants for whom there is missing data at 48 and 96 weeks in the maraviroc and non-maraviroc assigned groups
- e) Proportion of participants reporting adverse events at 48 and 96 weeks in the maraviroc and non-maraviroc assigned groups
- f) Level of self-reported adherence to the study drug at 48 and 96 weeks in those allocated to the maraviroc group

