### 7.7 Withdrawal criteria

A subject is free to withdraw from the study at any time. In addition, the Investigator may decide, for reasons of medical prudence, to withdraw a subject. If a subject discontinues study medication dosing, every attempt should be made to keep the subject in the study and continue to perform the required study-related procedures and follow-up procedures. If this is not possible or acceptable to the subject or Investigator, the subject may be withdrawn from the study.

Study medication may also be discontinued in the following instances:

1. If the subject withdraws his/her consent.
2. If the investigator considers in the interest of the subject (i.e. intercurrent illness, unacceptable toxicity) that it is best for them to withdraw their consent.
3. The subject fails to comply with the protocol requirements or fails to cooperate with the investigator.
4. Pregnancy during the course of the study.

The date and reasons for the withdrawal will be clearly stated on the subject's eCRF and source document. Every attempt should be made to arrange follow up visits for subjects who are withdrawn from the trial (including where individuals fall pregnant).

Subjects withdrawing from the trial may be replaced if considered necessary by the Chief Investigator.

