### 8.11 Assessment of compliance

Aim: To describe how compliance will be assessed

Participant adherence to MVC will be assessed through:

- a) Self reporting of doses of MVC taken via a diary card
- b) Pill counting at each visit by a pharmacist/research team member and recording of the number of pills returned

Participants will bring in all pill bottles at each study visit. The total number of IMP pills remaining at each visit will be counted and, then returned to the participant to take until the bottle is finished.

The percentage of IMP compliance for each participant will be calculated. Where this figure is <80%, this will lead to likely withdrawal from the study although this will be at the discretion of the PI. Where a discrepancy exists between self reported compliance and compliance identified via pill counting, any decision to withdraw the participant will rest with the study PI.

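### Stopping maraviroc has no primary measure of its own: retention (c) does not register it, and adherence (f) does so only under a scoring rule the protocol leaves open

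*Protocol*

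**What the plan says.** Protocol section 3.1 makes feasibility and acceptability of adding maraviroc to background therapy the primary objective, and says that a confirmed finding will support a larger placebo-controlled trial. Section 3.3 lists six measures: recruitment proportion, monthly recruitment, retention, missing data, adverse events and adherence.

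Two of them bear directly on this point:

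- Measure (c) is "Participant retention in the study at 48 and 96 weeks in the maraviroc and non-maraviroc assigned groups". Section 10.3.2 adds the expectation: "This is expected to be at least 65% (cf 35% discontinuation in the MOTIVATE study [9".
- Measure (f) is "Level of self-reported adherence to the study drug at 48 and 96 weeks in those allocated to the maraviroc group", expected to exceed 90%.

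Four other provisions decide what these measures will show:

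- Section 7.7: "If a subject discontinues study medication dosing, every attempt should be made to keep the subject in the study".
- Section 8.11 has two sources for adherence, a diary card and "Pill counting at each visit by a pharmacist/research team member and recording of the number of pills returned". It also says that compliance below 80% will probably lead to withdrawal from the study, at the local investigator's discretion.
- Section 10.3.2 analyses available cases on intention-to-treat principles and includes everyone randomised, even those later withdrawn.
- Section 10.4: where data are missing, "only available data will be included in the analyses".

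**The concern.** In a pilot about acceptability, stopping the added drug is the most direct sign that it was not acceptable, and the stopping rate is a figure the larger trial will need for planning. No primary measure is defined as that rate.

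Measure (c) looks as if it were meant to serve, because its expectation is the complement of a discontinuation percentage. But it counts people in the study, and 7.7 separates being in the study from being on the drug. The better a site follows 7.7, the less (c) says about stopping. The same 65% also applies to the control arm, which has no study drug to stop.

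Measure (f) could carry the information, but the text supports two readings of it. The choice of primary measures is made in the protocol itself, in 3.3 and 10.3.2, so this is not merely detail awaiting an analysis plan.

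**Working it through.** **Inputs.** Section 10.1 sets 30 per group: "Assuming an attrition rate of 33%, a target of 30 individuals will be recruited per group [23", so as to leave a sample "with 20 patients in each group for the analysis". From 10.3.2: (c) at least 65%, (d) missing data below 20%, (e) adverse events below 10%, (f) above 90%. One input is assumed and not in the protocol: people still on maraviroc report 95% adherence on average.

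**The plan's own figures.** 1 − 0.35 = 0.65, so the 65% expectation is exactly the complement of the 35% discontinuation figure. 20 / (1 − 0.33) = 29.9, rounded up to 30 per group. Both reproduce.

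**Scenario 1: 10 of 30 stop and all stay in follow-up, as 7.7 asks.** Ten is close to 35% of 30 (10.5).

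- (c) = 30/30 = 100%, which meets 65%.
- Still on maraviroc = 20/30 = 66.7% (exact 95% CI 47.2% to 82.7%). No primary measure reports this.
- (d) need not change, because these people attend their visits.
- (f), mean over diary cards from those still dosing = 95%, which meets 90%.
- (f), mean over all allocated with stoppers at zero = 0.95 × 20/30 = 63.3%, which does not. Even with perfect adherence in the other 20, it is 1.00 × 20/30 = 66.7%.

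**How few stoppers separate the two readings.** With the rest at 95% and stoppers at zero, one stopper gives 0.95 × 29/30 = 91.8% and two give 0.95 × 28/30 = 88.7%. The second stopper takes (f) below 90% on one reading. On the other, (f) stays at 95% however many stop.

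**Scenario 2: 10 stop but are followed, and 10 others are lost.** (c) = 20/30 = 66.7%, still above 65%, while 10/30 = 33.3% are on the drug.

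**Scenario 3: the same 10 stoppers are withdrawn under 8.11.** (c) = 20/30 = 66.7%, which still meets 65%. (d) = 10/30 = 33.3% if withdrawn people count as missing, above 20%. So identical drug-taking gives (c) of 100% or 66.7%, depending on whether 7.7 or 8.11 governs.

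**Adverse events.** If stopping is for intolerance and an event is recorded, 3/30 = 10% already fails to be below 10%, and 10/30 = 33%. If stopping is for pill burden, (e) need not move.

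**The case against.** The tempting stronger reading is that discontinuation is invisible to every primary measure, so that the pilot could declare the drug acceptable after a third of the arm had stopped. The documents do not support that, for four reasons.

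- Measure (f) is defined by allocation, and 10.3.2 includes everyone randomised. A followed person known to have stopped has a known adherence of zero, not a missing value. Section 7.6 schedules adherence assessment at the 24-weekly visits with no exception for people off drug, and 7.7 asks that study procedures continue. That stoppers cease completing diary cards is therefore an assumption.
- Someone who stops for intolerance will normally have an adverse event recorded, so (e) would move.
- Pill-count compliance below 80% may lead to withdrawal under 8.11, which turns some stoppers into losses in (c).
- The benchmarks are worded as expectations. No pass/fail rule is given, so a declaration of feasibility is an inference from 3.1.

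All of this stands and limits the point. It does not remove it. The sentence in 10.3.2 that invokes intention to treat also restricts analysis to available cases, and 10.4 repeats the restriction, so the zero-scoring reading is allowed but not stated. Measure (e) and the 8.11 rule miss people who stop for reasons such as pill burden, which 10.3.2 itself expects to deter recruits, and who are then kept in follow-up. Even with zeros, one blended adherence figure cannot separate stopping from missed doses.

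Two limits remain. Whether the cited 35% meant stopping the drug or leaving the study cannot be checked from the protocol. The flow diagram is not shown and may tabulate discontinuations, though it is not a primary measure.

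**Conclusion.** The concern holds in limited form. Discontinuation of maraviroc has no primary measure; (c) counts followed stoppers as retained although its expectation is set against a discontinuation figure; and (f) captures stopping only under a rule the text does not fix. With a third of the arm stopping and staying in follow-up, (c) reads 100% against 66.7% on drug, and (f) reads 95% or 63%. Those (f) values rest on the assumed 95% in people still dosing and on (f) being summarised as a mean; the (c) value assumes that nobody is withdrawn under 8.11.

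It does not follow that every primary measure would miss the problem or that the pilot is bound to reach a wrong conclusion. This is a worthwhile, inexpensive improvement to what the pilot can say about acceptability, not a flaw that invalidates it.

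**What to change.** In 3.3 and 10.3.2, add the proportion of those allocated to maraviroc who are still taking it at 48 and 96 weeks, with reasons for stopping. Set the benchmark derived from the 35% figure against this measure, after confirming in the cited trial that the figure refers to stopping the drug.

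State that (f) covers everyone allocated to maraviroc, with doses after permanent discontinuation counted as not taken, and report the pill-count adherence already collected beside self-report.

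Sections 7.7 and 8.11 must be reconciled on whether people who stop or take little of the drug remain in the study, because (c) depends on the answer. Which rule should apply is for the trial team.

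The cost is wording in these sections and a drug stop date and reason in the eCRF, recorded separately from study withdrawal. Pill counts and dispensing are already part of the protocol, and no dose or visit changes. The reported adherence figure will probably look less favourable.
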